# Effect of a qigong intervention program on telomerase activity and psychological stress in abused Chinese women: a randomized, wait-list controlled trial

**DOI:** 10.1186/1472-6882-14-300

**Published:** 2014-08-15

**Keywords:** Qigong, Violence, Telomerase, Perceived stress, Abused women, Intimate partner violence (IPV), Intervention, Depression, Chinese, Randomized controlled trial (RCT)

## Abstract

**Background:**

Abused women, who suffer from chronic psychological stress, have been shown to have shorter telomeres than never abused women. Telomere shortening is associated with increased risk of cell death, and it is believed that adopting health-promoting behaviors can help to increase the activity of telomerase, an enzyme that counters telomere shortening. Qigong is an ancient Chinese mind-body integration, health-oriented practice designed to enhance the function of *qi*, an energy that sustains well-being. Therefore, an assessor-blind, randomized, wait-list controlled trial was developed to evaluate the effect of a qigong intervention on telomerase activity (primary objective) and proinflammatory cytokines, perceived stress, perceived coping, and depressive symptoms (secondary objectives) in abused Chinese women.

**Methods/Design:**

A total of 240 Chinese women, aged ≥18 years, who have been abused by an intimate partner within the past three years will be recruited from a community setting in Hong Kong and randomized to receive either a qigong intervention or wait-list control condition as follows: the qigong intervention will comprise (i) a 2-hour group qigong training session twice a week for 6 weeks, (ii) a 1-hour follow-up group qigong exercise session once a week for 4 months, and (iii) a 30-minute self-practice qigong exercise session once a day for 5.5 months. The wait-list control group will receive qigong training after the intervention group completes the program. Upon completion of the qigong intervention program, it is expected that abused Chinese women in the intervention group will have higher levels of telomerase activity and perceived coping and lower levels of proinflammatory cytokines, perceived stress, and depressive symptoms than will abused Chinese women in the wait-list control group.

**Discussion:**

This study will provide information about the effect of qigong exercise on telomerase activity and chronic psychological stress in abused Chinese women. The findings will inform the design of interventions to relieve the effects of IPV-related psychological stress on health. Also, the concept that health-promoting behaviors could slow down cellular aging might even motivate abused women to change their lifestyles.

**Trial registration:**

Current Controlled Trials NCT02060123. Registered February 6, 2014.

## Background

Intimate partner violence (IPV), also known as domestic violence, involves assaultive and coercive power and control tactics used by a current or former partner to cause emotional, physical, and/or sexual harm [1]. While both men and women can be victims of IPV, most victims are women [2]. Moreover, the female partner receives the majority of IPV-related injuries [2].

IPV is a global problem. For example, the World Health Organization estimates that from 10% to 50% of women worldwide have been physically or sexually assaulted by their intimate partners at some time in their lives [3]. Additionally, overwhelming evidence indicates that IPV is linked to adverse health outcomes [4, 5] and that it is a greater health burden than smoking and obesity [6].

Despite the abundant evidence linking IPV to negative health outcomes [4], the mechanisms underlying this association are not fully understood[7]. It is often assumed that the greater morbidity experienced by abused women is due to the chronic psychological stress of having to live in an atmosphere of fear, shame, and coercion [5]. More specifically, a recent study suggests that IPV-related stress may accelerate cellular aging, which in turn may attenuate normal bodily functions and lead to greater morbidity [8].

Cell growth is essential to the continuity of living organisms. Cellular senescence or aging is a state of permanent cell growth arrest that is believed to be a damage response to a variety of stressors [9]. Excessive accumulation of senescent cells may lead to organ dysfunction. One of the basic mechanisms by which normal somatic cells enter into senescence involves continuous shortening of a chromosomal terminal structure called the telomere. Telomeres are nucleoprotein structures at the ends of chromosomes, and their function is to protect the chromosome ends from deterioration or fusion with other chromosomes. Telomeres generally shorten with aging, but the shortening may be accelerated in the presence of chronic psychological stress [10]. A cellular enzyme termed telomerase elongates telomeres by adding DNA hexameric repeats to restore the length of the telomere [11]. Accelerated telomere shortening occurs in cells with lowered telomerase activity and in those under oxidative stress. Accelerated telomere shortening may be a predictor of early morbidity and mortality [8].Thus, telomeres and telomerase play prominent roles in maintaining normal cell function and genome integrity [11, 12].

Various forms of chronic psychological stress reportedly lead to telomere shortening. In one study, the perceived level of psychological stress in mothers who took care of children with chronic illness was associated with shorter telomeres, higher oxidative stress levels, and lower telomerase activity levels [10]. This association between chronic psychological stress and accelerated telomere shortening has been also observed in individuals with mood disorders including major depression, bipolar depressive disorder, and anxiety disorder [13–17] and in caregivers of patients with Alzheimer’s disease [18]. Study participants with a history of childhood maltreatment or other adversities have exhibited shorter telomeres than those without such experiences [16, 19]. In another study, women with a history of intimate partner abuse had shorter telomeres than did never abused women [8].

Several researchers have suggested that telomerase activity may be increased by health-promoting behaviors such as physical exercise [20, 21], intensive meditation training [22, 23],yogic meditation[24, 25], and comprehensive lifestyle changes (including regular physical exercise and psychological stress counseling) [26]. More recently, Chinese people with chronic fatigue or chronic fatigue syndrome were shown to have higher telomerase activity levels after undergoing qigong exercise intervention than did the control group, supporting the speculation that qigong may enhance telomerase activity by promoting mindfulness and managing stress [27].

### Health benefits of qigong

Qigong refers to the cultivation or enhancement of *qi*. According to Traditional Chinese Medicine, *qi* is an energy that sustains human well-being and assists in healing [28]. Qigong originates from ancient healing and medical practices in Asia and dates back more than 5000 years. It comprises a series of orchestrated practices including body postures such as standing or sitting, the performance of a range of simple movements, breath practice to accompany the postures or movements, and meditation to achieve a focused state of relaxed awareness. All of these practices are designed to enhance the function of *qi* through the attainment of deeply focused and relaxed states [28]. Many forms of qigong have been developed over the centuries. Some are designed for spiritual practice, while others are designed to enhance martial art skills. Still others were designed for general health enhancement, including the Eight Brocade (or *baduanjin*), which is the form of qigong reported in this paper. By evoking body–mind integration, health-oriented qigong practices (including the Eight Brocade) are thought to activate self-healing by stimulating the balanced release of endogenous neurohormones and other natural health recovery mechanisms [28].

In a systematic review of randomized controlled trials examining the health benefits of qigong, anxiety was found to be significantly lower among participants practicing qigong than among those in the control group engaged in active exercise [29–31]. The severity of depression was also significantly lower after qigong than in an inactive control group engaged in newspaper reading [32]. However, non-statistically significant changes in depression were found when qigong was compared with a control group of subjects who underwent no qigong training during the same study period [33] and with a control group engaged in exercise [29, 34]. Significantly lower norepinephrine, epinephrine, and cortisol blood levels were found in the qigong group than in a wait-listed control group [35]. Qigong was also shown to improve chronic fatigue and increase telomerase activity in a study of Chinese patients, as described earlier [27]. Taken together, the above findings suggest that qigong may have beneficial health effects. Specifically, the protective effect of qigong as a mind–body intervention on telomere and telomerase activity should be further investigated. If the meditation component of qigong protects telomeres or telomerase activity by reducing chronic psychological stress, as has been suggested for other meditation training [36], we would expect to find that qigong intervention also has protective effects on telomere or telomerase activity in people experiencing chronic psychological stress. IPV has long been recognized as a potent source of chronic psychological stress [37]. An earlier study revealed that abused women had significantly shorter telomeres than did never-abused women [8], suggesting a link among IPV, chronic psychological stress, and accelerated cellular aging. However, evidence on the optimal telomere or telomerase activity protection measure in abused women is still lacking.

This study protocol describes a randomized controlled trial that evaluates the effect of a qigong intervention on telomerase activity and other parameters in abused Chinese women. The decision to use qigong in this study is based on the findings of our earlier intervention [38] in which Chinese medicine dietary regimens based on individual health assessments by a Chinese medicine practitioner were provided to abused women in a shelter in Hong Kong. An imbalance and disharmony of *qi* was found to be the root cause of the women’s health symptoms, the most common being insomnia, headache, palpitation, and fatigue. Furthermore, the participants who adhered to the intervention, namely the individualized Chinese medicine dietary regimen, reported significantly greater improvement in their health symptoms [38] than did participants who did not adhere to the regimen. These results indicate that the Chinese abused women were receptive to engaging in health-promoting behaviors based on the concepts of Chinese medicine and benefited from an intervention that promoted the balance and harmony of *qi*. We have therefore decided to adopt qigong as an intervention to promote abused Chinese women’s health and well-being.

### Aims

The primary aim of this randomized, wait-list controlled trial is to evaluate the effect of a qigong intervention on telomerase activity in Chinese women with a history of IPV. The secondary aim is to evaluate the effect of the intervention on the women’s levels of proinflammatory cytokines, perceived stress, perceived coping, and depressive symptoms.

We hypothesize that upon completion of the qigong intervention, abused Chinese women in the intervention group will have higher telomerase levels as measured by telomerase activity in peripheral blood mononuclear cells, lower proinflammatory cytokine levels as measured by tumor necrosis factor-alpha (TNF-alpha) and interleukin-6 (IL-6) in peripheral blood mononuclear cells, lower perceived stress scores as measured by the Perceived Stress Scale, higher perceived coping scores as measured by the Perceived Coping Scale, and lower depressive symptoms scores as measured by the Beck Depression Inventory version II than will women in the wait-list control group.

## Methods/Design

This randomized, wait-list controlled study will comprise two arms: an intervention group that will undergo immediate treatment (qigong intervention) and a wait-list control group that will undergo delayed treatment (the same qigong intervention, but provided after the intervention group has completed the immediate treatment). Thus, this randomized, wait-list controlled design will allow all study participants to eventually undergo the intervention while also controlling for variables that could cause spurious causality. The justification for using a wait-list control group in this study is that (i) the anticipation of undergoing qigong training in the near future can act as an incentive for the control group to participate in the study and (ii) qigong can be provided to both groups without increasing the risk of treatment contamination.

### Participants

Chinese women will be eligible to participate if they are:≥18 years of age,willing to undergo the qigong intervention,available for all testing points,receptive to random allocation, andconfirmed to have been abused by an intimate partner within the past three years based on the Chinese Abuse Assessment Screen (C-AAS).

Chinese women will be excluded if they:have participated in qigong training or other mind–body interventions within the previous 6 months,have serious medical conditions that might limit their participation in qigong exercise (based on our previous experience, such conditions include cancer, severe obesity, narcolepsy, major depressive disorder, and schizophrenia),have psychiatric disorders,use medication or other psychological intervention for stress, orhave been abused by someone other than their intimate partner.

### Sample size

Sample size calculation will be based on a primary comparison of telomerase activity levels between the intervention and control groups. Based on a previous study that examined the effect of qigong on telomerase activity [27], the standard deviation will be set at 0.2. As in the study by Ho et al. we anticipate approximately 0.05 to 0.10 units of improvement in telomerase activity secondary to qigong. Thus, 113 subjects per group are required to detect a difference of at least 0.075 units between the two groups with 80% power and a ≤5% chance of a false-positive error. Allowing for a small rate of attrition, 240 women will be recruited and randomly assigned to either the intervention group (treatment condition, n = 120) or the wait-list control group (control condition, n = 120).

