### Intervention

The qigong intervention in this project is based on the intervention tested by our team members ([name], Ho) in an earlier study that involved participants with chronic fatigue and achieved positive outcomes [27]. The intervention comprises (i) group learning and practice: a 2-hour qigong exercise training session provided by a qigong master twice a week for 6 consecutive weeks (total, 24 hours), (ii) weekly group follow-up: a 1-hour qigong exercise session provided by a qigong master once a week for 4 consecutive months (total, 16 hours) after the group learning and practice, and (iii) self-practice: a 30-minute qigong exercise session performed by each individual participant once a day for the whole intervention period (total, 63 hours). Each participant will perform a total of 103 hours of qigong during the 5.5-month intervention period.

For each of the 2-hour qigong exercise training sessions during the 6-week group learning and practice periods, the activities will include (i) a brief introduction to the basic theories of traditional Chinese medicine and the physiology of mind–body connections, (ii) gentle movement or body stretching in a standing posture to facilitate a harmonious flow of *qi* along the energy channels, and (iii) qigong exercise training delivered by an experienced qigong master.

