**Flow diagram of intervention/wait-list control and data collection points.**

Maintaining minimal attrition throughout the 5.5-month period will be important. Therefore, we intend to use the same field tracking strategies that we used in our previous project [40], which achieved zero attrition. Specifically, we will use systematic field tracking strategies that model the systemized tracking methodology used by McFarlane et al. to achieve a high retention rate [41]. Details of the tracking strategies, which have proven effective in providing early warnings about possible drop-outs, were previously reported [40].

Furthermore, we shall implement the following additional measures to reduce attrition and enhance the participants’ adherence to the intervention:Weekly group follow-up sessions provided by a qigong master to reinforce learning and remedial teaching and motivate the participants to engage in learning and practiceFormation of small subgroups to promote group cohesion and supportElection of a peer leader of each subgroup to enhance group communication and sharingRecording of qigong and other exercises undertaken on a record card, which will be submitted to our researcher at the weekly group follow-up sessions to check each participants’ self-practice complianceMonthly health education talks unrelated to the qigong intervention for participants in the wait-list control groupAll participants will be informed at the time of recruitment and regularly throughout the study that upon successful completion of the project, they will receive a health report based on the data collected as well as a DVD and book on *baduanjin.*

Finally, we will provide an incentive to the participants in the form of food coupons to show our appreciation of their time and efforts.

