#### Primary analysis

The telomerase activity upon completion of the intervention (i.e., T2) between the intervention and wait-list control groups will be assessed by regression analysis with adjustment of baseline values. Residuals will be checked to ensure the adequacy of the method. Additionally, the change in telomerase activity from baseline (T0) to postintervention (T2) will be assessed by a paired t-test. The intention-to-treat principle will be adopted, and all study subjects will be included in the analysis. Missing values will be replaced by the last observed values.

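### Qigong is taught in classes with peer-led subgroups, but the sample size and primary regression allow for no within-class correlation; if it is positive, intervals are too narrow and type I error exceeds 5%

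*Protocol article*

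**What the plan says.** All references are to the protocol article.

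- **Randomization and blinding:** individual women are allocated by permuted blocks.
- **Intervention:** the group learning phase is "a 2-hour qigong exercise training session provided by a qigong master twice a week for 6 consecutive weeks", which makes 12 sessions. A weekly one-hour group session follows for four months, totalling 16 hours, so 16 sessions.
- **Procedures (retention and adherence measures after Figure 1):** these include "small subgroups to promote group cohesion" and mutual support, with a peer leader elected in each subgroup.
- **Procedures (control arm):** control women are offered monthly health education unrelated to qigong. Whether it runs in fixed groups is not stated.
- **Sample size:** "the standard deviation will be set at 0.2"; "we anticipate approximately 0.05 to 0.10 units of improvement in telomerase activity secondary to qigong"; "113 subjects per group are required to detect a difference of at least 0.075 units between the two groups with 80% power", with "a ≤5% chance of a false-positive error". Recruitment is set at 240, or 120 per arm, to cover attrition.
- **Primary analysis:** telomerase activity at T2 "will be assessed by regression analysis with adjustment of baseline values". No class, subgroup or instructor term is named.
- **Secondary analysis:** a linear mixed model with a random intercept. The unit of that intercept is not named, and no class level is mentioned.

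**The concern.** This is a partially nested design: independence is created by randomisation, then weakened in one arm by how the treatment is delivered. Women in the same class share 28 sessions and their peers. The subgroups exist so that members influence one another's attendance and practice, which is a plausible route to correlated outcomes.

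A regression that treats every woman as an independent unit attributes any shared class component to individual variation. The standard error of the treatment effect is then too small, and a nominal 5% test rejects too often. Adjusting for baseline reduces residual variance but does not model the shared component, and enrolling more women into the same structure does not remove it either. The main stake is therefore the validity of the primary confidence interval and p-value. Power is a secondary stake.

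**Working it through.** **1. Reproduce the plan's figure.** Inputs from Sample size: difference 0.075, SD 0.2, power 80%, alpha 0.05. Two-sided testing is inferred, because one-sided gives 88.

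n per arm = 2 × [(1.960 + 0.842) × 0.2 / 0.075]² = 111.6, so 112 by the normal approximation. The two-sample t-test gives 79.8% power at 112 and 80.1% at 113. The stated 113 is therefore the independent-observations t-test figure and contains no design effect.

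**2. Add clustering in the qigong arm only.** Class size m and ICC are assumptions, since neither is in the article. The formulas also assume equal class sizes and total SD 0.2.

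- DE = 1 + (m − 1) × ICC
- Var(difference) = 0.04 × (DE + 1) / 113
- True SE / independence SE = √[(1 + DE) / 2]
- Type I error of the test that ignores classes = 2 × [1 − Φ(1.96 / SE ratio)]
- Power = Φ(0.075 / √Var − 1.96)

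Worked case, m = 20 and ICC 0.05:

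- DE = 1 + 19 × 0.05 = 1.95.
- SE = √(0.04 × 2.95 / 113) = 0.0323, against 0.2 × √(2/113) = 0.0266 under independence. The ratio is 1.214.
- Type I error = 2 × [1 − Φ(1.96 / 1.214)] = 10.7%.
- Power = Φ(0.075 / 0.0323 − 1.96) = 64%.

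| Class size | ICC | SE ratio | Type I error, classes ignored | Power at 113 per arm |
|---|---|---|---|---|
| 8 | 0.01 | 1.017 | 5.4% | 79% |
| 8 | 0.02 | 1.034 | 5.8% | 78% |
| 8 | 0.05 | 1.084 | 7.1% | 74% |
| 20 | 0.01 | 1.046 | 6.1% | 77% |
| 20 | 0.02 | 1.091 | 7.2% | 73% |
| 20 | 0.05 | 1.214 | 10.7% | 64% |
| 30 | 0.01 | 1.070 | 6.7% | 75% |
| 30 | 0.02 | 1.136 | 8.4% | 70% |
| 30 | 0.05 | 1.313 | 13.6% | 57% |

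Power under independence on the same normal basis is 80.5%.

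**3. Offsets to the power loss.**

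- *All 120 per arm retained* (replace 113 by 120): 82.8% under independence; 81.1% at m = 10, ICC 0.01; 80.2% at m = 8, ICC 0.02; 79.3% at m = 20, ICC 0.01.
- *Baseline adjustment*, for which the 113 takes no credit: the variance is multiplied by (1 − ρ²), taking the ICC to apply to the residual. With an assumed baseline correlation ρ = 0.5 and 113 per arm, power is 90.2% without clustering, 83.7% at m = 10, ICC 0.05, and 76.4% at m = 20, ICC 0.05.

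Neither offset changes the SE ratio, so neither changes the type I error column.

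**4. Cost of few classes.** At m = 30 there are 113 / 30 ≈ 3.8 classes. With ICC 0.05:

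- Variance of the qigong mean: 0.04 × 2.45 / 113 = 0.000867. Variance of the control mean: 0.04 / 113 = 0.000354.
- Satterthwaite df = (0.001221)² / [0.000867² / 2.77 + 0.000354² / 112] ≈ 5.5.
- Power from the noncentral t is then about 43%, not the 57% of the normal approximation.

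Even at ICC 0, always using these degrees of freedom at m = 30 gives about 73%.

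**The case against.** The case on the other side has real substance.

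- **The harm is conditional.** Telomerase activity is a laboratory assay read blind to allocation. The article gives no ICC, class size, number of classes or number of masters. A reader might infer that the intervals are too narrow as a matter of fact; the article does not support that. This stands, and the point is worded conditionally.
- **Power may hold.** A reader might also infer that 80% power is reached only if the ICC is exactly zero. That is wrong: power is 81.1% with 120 per arm at m = 10, ICC 0.01, and 83.7% at 113 with m = 10, ICC 0.05 and an assumed baseline correlation of 0.5. This stands.
- **Some shared influences are uncertain.** If one master teaches every class, the master creates no between-class variance. Calendar time is not specific to the qigong arm, because allocation is blocked and both arms are assessed at the same points. This stands; the argument rests on shared sessions and on subgroups built for cohesion.
- **Small groups do less damage.** At m = 8 with ICC 0.01 or 0.02, type I error is only 5.4% or 5.8%. This stands, and is why that case is in the table.
- **Model detail may sit in a document not shown.** This stands only in part. The article itself fixes the sample size basis and names the primary model, and a class effect would change the primary standard error, not just fill in detail.

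**Conclusion.** The point holds in conditional form. Group delivery is documented, the 113 is an independence figure, and the stated primary regression has no class term. With any positive within-class correlation, that model understates the standard error and its type I error exceeds the stated 5%. Over ICC 0.01 to 0.05 the type I error runs from 5.4% (classes of 8) to 13.6% (classes of 30), and neither baseline adjustment nor the attrition margin corrects it.

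Power is the weaker half. It is lower than under independence, but net power below 80% is possible, not shown. The 113 is not an arithmetic error.

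The figures rest on assumed ICCs and class sizes, equal classes, clustering in the qigong arm only and the normal approximation. Clustering of the control sessions, or small-sample degrees of freedom, would lower power further.

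**What to change.** 1. Record the class, and the subgroup, of each woman in the qigong arm at delivery, since membership may be hard to reconstruct later.
2. Fit the primary and secondary models with a class random effect in the qigong arm, arm-specific residual variance, and Satterthwaite or Kenward-Roger degrees of freedom. Treat control women as singletons unless their health education sessions run in fixed groups.
3. In Sample size, give the planned class size, state that 80% power assumes uncorrelated outcomes within a class, and show power for ICC 0.01 to 0.05 at that size.

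**Cost:** an added data field or two and some model wording, with no extra enrolment. The downside is wider intervals and a lower stated power. With many small classes this is modest. With only a few large ones it is substantial, because the class variance is poorly estimated and few degrees of freedom remain, so class size and number should be settled together with the model.
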